### Test site selection and characterization

#### Selection of the test sites

First, we aimed to identify areas featuring a high variation in traffic noise at different times of the day to compare the benefits of walking in the same area with high and low traffic noise exposure. For this purpose, we analyzed traffic data from the city of Zurich, Switzerland, on the number of motorized individual vehicles as a proxy for traffic noise in the corresponding area [91]. The city of Zurich provides daily updated data on motorized individual vehicles in Zurich, measured at 97 measurement points of the traffic department (for the exact locations of the measurement points, see City of Zurich traffic department [92]). We randomly chose the working days of one week in 2021 (05.31.2021–06.04.2021) and calculated the mean number of vehicles per hour of the working days of this week from 8:00 a.m. to 8:00 p.m. We then checked the variances to identify the places with the highest hourly variation. Using this approach, we did not find settings with a stable time and a sufficiently high traffic noise variation of at least 10 dB between 8:00 a.m and 8:00 p.m. Thus, we decided to instead compare urban built and forest settings with widely constant noise conditions during the afternoon, featuring either high or low road traffic noise, which are as similar as possible between locations with respect to other characteristics besides noise (e.g., amount of vegetation, density of buildings, inclination, and presence of water).

To minimize the risk of systematically confounding loud and quiet settings with other variables that might potentially vary between settings with different noise levels (e.g., inclination in the walking route and flowing water in the surroundings), we selected three settings per condition in Zurich (three loud and three quiet urban built settings as well as three loud and three quiet forest settings). The test settings were selected stepwise. We incorporated geographic information system (GIS) data and GIS methods to select potential test sites and considered two important factors: road traffic noise and vegetation.

The road traffic noise data were obtained from the Swiss-wide noise database sonBASE for the year 2015 [93], and we used the mean exposure values for the daytime period between 6:00 a.m. and 10:00 p.m. SonBASE provides so-called rating sound levels (*Lr*) according to the Swiss Noise Abatement Ordiance (NAO) [94], with a spatial resolution of 10 × 10 m. The *Lr* corresponds to the A-weighted equivalent continuous sound pressure level (*L*_Aeq_) on a yearly average for road traffic, railway and aircraft noise, potentially with level corrections depending on the noise source and traffic density (for details see NAO [94]). To choose potential settings with similar noise characteristics, road traffic noise was divided into three noise classes (N1: Lr of daytime < 35 dBA, N2: Lr of daytime at 35–45 dBA, N3: Lr of daytime > 45 dBA). Areas with railway and aircraft noise *L*_r_ > 30 dB were excluded. Vegetation was characterized using its height (vegetation height model, VHM, [95]) as well as its abundance expressed by the normalized difference vegetation index (NDVI) [96], with NDVI values ranging from − 1 to 1 (NDVI > 0 shows vegetation), and VHM values given in meters. We calculated the median and standard deviation of the NDVI from all available cloud-free Sentinel-2 satellite images available between April and October for the years 2016–2019. Three classes of vegetation types were distinguished. To build the classes, we aimed to distinguish areas of similar characteristics in terms of NDVI and VHM based on unsupervised classification, using the Iso Cluster [97] and Maximum Likelihood Classification tools [98]. The classes were as follows: G1: hardly green spaces (mostly artificial surfaces); NDVI median = 0.07–0.24, VHM median = 0 m; G2: green spaces with low vegetation (mostly grass, with possible single shrubs and very small trees); NDVI median = 0.55–0.66, VHM median = 0.25–0.43 m; G3: green spaces with abundant and high vegetation (composed of trees, shrubs, and grass); NDVI median = 0.67–0.70, VHM median = 17.71–23.06 m.

The combinations of the three noise-based and the three vegetation-based categories indicated the potential test settings to be explored. In the next step, potential test sites were explored further via satellite images, inspecting the size of the areas (large enough for 30-min walks), vegetation, the existence of continuous sidewalks in the urban built areas, density, and height of buildings. Areas with water bodies or bridges were excluded, and we avoided steep road or path sections to minimize differences in exercise intensity. Finally, the remaining settings were inspected on-site. To avoid differences in social interaction between the settings, places with construction work were excluded as were places likely to feature large numbers of people. Potential walking routes were developed for suitable settings, and the sound pressure levels during the entire 30-min routes of the potential test settings were recorded during various walks at different times of the afternoon to inspect if the settings differed sufficiently in terms of noise. We aimed at a difference of 10 dB between loud and quiet settings. All of these criteria were used only for identifying potential and selecting the final test sites. In the final analysis, the actual measured noise levels during the walks will be taken as inputs for the statistical analysis.

#### Characterization of the final test sites

Figure 3 shows the locations of the starting points of the walking routes in the final test sites in the city of Zurich. For the exact coordinates of the starting points, see the file on “Locations of the starting points of the walking routes in the test settings” in the Supporting Information. The GPS files of the walking routes can also be found in the supporting information.

**Fig. 3 Fig3:**
[figure not shown]
Locations of the final test settings. 1) [name]. 2) [name]. 3) [name]. 4) [name]. 5) [name]. 6) [name]. 7) [name]. 8) [name]. 9) [name]. 10) [name]. 11) [name]. 12) [name]. Basemap: swisstopo. 2020; Orthophoto (SWISSIMAGE 10) [99]

After selecting the final test settings, we performed a post-hoc classification of their vegetation and sound characteristics in the final test settings. For predicting vegetation, we calculated NDVI and VHM along each walking route with 50-m wide buffer zones on both sides of the lines. Table 1 shows a visual impression of the test settings and gives information on the vegetation characteristics of the respective walking routes. The locations for the two pictures on each route were chosen to be as characteristic as possible in terms of the visual and acoustical impressions of the walk.

**Table 1 Tab1:** Characterization of vegetation in the final test sites

**Setting number**	**Picture place 1 in setting**	**Picture place 2 in setting**	**VHM**^**a**^** in meter on walking route with 50 m buffer**		**NDVI**^**b**^** on walking route with 50 m buffer**	
			***M***	***SD***	***M***	***SD***
1: UBHT^c^			1.42	3.33	0.35	0.13
2: UBHT			1.47	3.19	0.38	0.12
3: UBHT			1.63	3.27	0.37	0.14
4: UBLT^d^			2.18	4.49	0.28	0.13
5: UBLT			1.58	3.48	0.37	0.12
6: UBLT			2.14	4.25	0.37	0.14
7: FHT^e^			20.65	9.99	0.68	0.07
8: FHT			18.36	11.05	0.69	0.06
9: FHT			16.17	10.20	0.66	0.09
10: FLT^f^			24.27	8.47	0.70	0.05
11: FLT			22.19	9.90	0.69	0.05
12: FLT			20.00	8.41	0.7	0.04

Notes. ^a^VHM values in meters, calculated along each walking path, with 50-m wide buffer zones on both sides of the lines. Mean and standard deviation for the average maximum height of vegetation in the buffer zone. ^b^Median and SD NDVI values, calculated along each walking path, with 50-m wide buffer zones on both sides of the lines. ^c^UBHT= urban built with high traffic noise. ^d^UBLT= urban built with low traffic noise. ^e^FHT = forest with high traffic noise. ^f^FLT = forest with low traffic noise

Table 2 provides the acoustical and soundscape characteristics of the final settings. The first column shows the *L*_Aeq_ recorded on the walking routes before starting with the data collection. For an additional post hoc classification of the sound environment in the settings, the acoustic impression was evaluated for the two locations at each test site in the afternoons of the same week in 2023 by a civil servant not familiar with the research questions of the present study. The sound environment was evaluated three subsequent times for the last 5 min at every location. When analyzing the results of the sound evaluation, the mean and standard deviation of all six sound evaluations (2 locations × 3 replicate evaluations) in each setting were computed. Table 2 shows the results of the major items for evaluating the sound environment. An additional result of the post hoc classification of the sound environment was that, in urban built and forest settings with high road traffic noise, road traffic noise was judged the most dominant sound source in all settings. In urban built settings with low road traffic noise, road traffic noise or sounds from humans were judged as the most dominant sound source. In forest settings with little road traffic noise, natural sounds and sounds from other than the three previously mentioned sound sources were judged as most dominant. As intended, urban built settings with high road traffic noise showed a higher *L*_Aeq_ and were judged to feature a higher extent of traffic noise than urban built settings with low road traffic noise. Equally, forest settings with high road traffic noise showed a higher *L*_Aeq_ and were judged to feature a higher extent of traffic noise than forest settings with low road traffic noise. Generally, *L*_Aeq_ was higher in urban built settings, compared to forest settings and the extent of traffic noise was similar in urban built and forest settings. For urban built sites with (very) little vegetation and low noise, we could not find suitable environments with the dBA thresholds that we chose at the beginning. Thus, the thresholds had to be adapted to the environments present in the area of Zurich. This is because we strived for high external validity. Loud and quiet are thus defined depending on the environment. As expected, the extent of natural sounds was generally higher in forest settings, compared to urban built settings.

**Table 2 Tab2:** Sound characterization of the final test sites

**Setting number**	***L***_**Aeq**_** on walking route**^a^		**Extent of traffic noise**^c^		**Extent of natural sounds**^d^	
	***M***	***SD***	***M***	***SD***	***M***	***SD***
1: UBHT^e^	68.71 (*n* = 3)^b^	3.55	3.50	0.55	1.83	0.41
2: UBHT	64.19 (*n* = 4)	1.67	2.50	0.84	1.83	0.41
3: UBHT	65.53 (*n* = 5)	1.33	3.00	0.00	1.00	0.00
4: UBLT^f^	58.42 (*n* = 4)	3.46	2.17	0.41	2.17	0.41
5: UBLT	57.53 (*n* = 5)	1.16	2.00	0.00	2.00	0.00
6: UBLT	48.74 (*n* = 2)	6.70	1.83	0.41	2.67	0.52
7: FHT^g^	64.30 (*n* = 6)	1.83	3.17	0.41	2.17	0.41
8: FHT	59.25 (*n* = 3)	1.11	3.67	0.52	2.33	0.52
9: FHT	59.55 (*n* = 4)	.87	3.50	0.55	2.17	0.41
10: FLT^h^	49.67 (*n* = 3)	1.80	1.83	0.75	3.33	0.52
11: FLT	49.98 (*n* = 3)	.61	1.17	0.41	3.50	0.55
12: FLT	49.98 (*n* = 4)	2.83	2.17	0.75	3.83	0.41

^a^L_Aeq_ of sound recording, measured on each route. ^b^Number of sound recordings in the setting. ^c^Extent to which traffic noise was heard during the last 5 min, responding on a Likert scale ranging from 1 (*not at all*) to 5 (*completely dominating*), evaluated by civil servant. ^d^Extent to which natural sounds were heard during the last 5 min, responding on a Likert scale ranging from 1 (*not at all*) to 5 (*completely dominating*), evaluated by a civil servant. ^e^UBHT urban built with high traffic noise. ^f^UBLT urban built with low traffic noise. ^g^FHT forest with high traffic noise. ^h^FLT forest with low traffic noise

For including noise as a predictor in the final statistical model, we will calculate the percentage of time in which traffic noise is the dominating sound source during each walk as well as the *L*_Aeq_ during the time in which traffic noise is the dominating sound source after having completed data collection.

### Participants and recruitment

Participants will be recruited by various means. A random sample of 7,000 people will be drawn from the residents’ registration office in the city of Zurich. The sample will be stratified over four age groups, 18–35, 35–50, 50–65, and > 65, to reach people of all ages. These participants will be invited to take part in the study by letter. In addition, students from the universities of Zurich (University of Zurich and Swiss Federal Institute of Technology Zurich) will be recruited via e-mail and by lecturers, who will forward the invitation to their students. The invitation to participate will also be distributed via local newspapers, local web portals, as well as at some of the authors' institution Empa. Furthermore, participants will be recruited through advertising with invitation flyers in public places in Zurich and via a study webpage. Finally, participants will be invited via the snowball sampling method, in which the researchers reach out to their social networks to distribute the invitation in Zurich. Participants will receive a remuneration of 50 CHF. Additionally, two massage vouchers amounting to 120 CHF each will be raffled anonymously among all participants who have completed the t1, t2, and t3 questionnaires. Individuals will be eligible for participation if they: (a) are 18 years and older; (b) are physically able to walk for half an hour at a moderate pace; (c) have no diagnosed hearing problems; (d) do not take cortisone for medical reasons; and (e) have a BMI < 35. The study has been approved by the Ethics Committee of the Swiss Federal Institute of Technology Zurich (Ref No. EK 2021-N-211 of 27.01.2022). The study results will be released to the participants and the public. All data will be identified with an identification number to maintain participant confidentiality. Access to the study data will be restricted to the study team, and all forms related to the study data will be kept in locked cabinets*.*

### Sample size calculation

A statistical power calculation was conducted for the restoration outcome scale as the primary outcome. A previous study, employing a similar design to the current study, was conducted by Tyrväinen et al. [14], who compared the restorative effects of exposure to a forest, a park, or an urban built environment using the restoration outcome scale. Participants sat in the respective environment for 15 min, followed by a 30-min walk. Based on the mean scores and standard deviations for the restorative outcome scale before and after the walk in the urban built environment and in the forest, reported by Tyrväinen et al. [14] (mean ROS urban built before = 4.56 (SD = 0.89), mean ROS urban built after = 4.2 (SD = 0.97), mean ROS forest before = 4.6 (SD = 0.84), mean ROS forest after = 5.16 (SD = 0.82)), the power for the current study was calculated using a simulation-based approach. For the simulation, a linear mixed effects model was used, taking group effects and participant effects into account by including a random intercept for participant groups as well as for individual participants. The required number of groups was estimated for a desired statistical power of ≥ 80%, calculating the number of simulations with a significant interaction effect of environment × time using R [100]. Power calculation showed that 19 groups with 1–6 participants per group are required to identify statistical differences between the conditions, assuming a power of ≥ 80% and an alpha level of 0.05. Thus, to accomplish an equal number of groups in urban built environments and forests, we are aiming for a minimum of 10 groups in urban built environments and 10 in forests.

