Although various earlier studies have compared the restorative effects of exposure to greenspaces versus urban built environments [18, 36–39], evidence of the effects of noise in this context is very limited. In their meta-analysis, Bowler and colleagues [36] compared the added benefits to health and well-being outcomes from activities such as walking and running in greenspaces versus synthetic (outdoor and indoor-built) environments. The results were mixed and revealed a paucity of good-quality studies. The authors concluded that well-designed studies are needed to further strengthen evidence and noted that differences between the benefits of greenspaces and urban built environments are less due to features of the greenspaces than to additional stressors in the urban built environment–one such stressor possibly being traffic noise. At the same time, Van Renterghem [31] discusses how vegetation can mitigate environmental noise perception, proposing a complex interplay between vegetation and noise factors for restoration.

In this context, we argue that although various earlier studies have compared the effects of exposure to greenspaces versus urban built environments, not enough attention has been given to potential confounding variables in previous studies. The greenspaces and urban built environments in earlier studies may have differed not only in terms of the extent of greenness of the compared environments, but also in terms of other variables. One particular variable in which environments might have differed is the extent of transportation noise (in particular road traffic noise) in different settings. Hence, differences in the effects attributed to greenness in previous studies may also be attributed to potentially detrimental (road traffic) noise effects in comparison settings, which potentially confounded previous results.

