### Outcomes

#### Primary outcomes

The primary outcomes are “perceived restoration”, measured with a self-report questionnaire and salivary cortisol as a physiological stress marker.

Perceived restoration will be assessed using a slightly modified version of the restoration outcome scale (ROS) [67]. The questionnaire was put in past tense, and participants will be asked to what extent the walk contributed to three items concerning relaxation and calmness (e.g., “I feel calmer after being here”), one item reflecting attention restoration (“my concentration and alertness clearly increased”), and two items indicating clearing one’s thoughts (e.g., “I was able to forget my everyday worries here”). The questionnaire has been translated into German, including a back translation into English by the internal translator of the Swiss Federal Research Institute WSL. Items are rated on a Likert scale ranging from 1 (*not at all*) to 7 (*completely*). The scale has been used in several previous studies examining the benefits of exposure to nature [14, 68, 69] and has been shown to have good internal consistency with a Cronbach’s alpha of .92 [67].

The physiological stress marker salivary cortisol is considered a reliable indicator for assessing hypothalamic pituitary adrenocortical (HPA) axis activity [62, 70]. Saliva samples will be collected using synthetic swabs (Sarstedt, Germany). For saliva collection, participants will place the swab in their mouth for 2 min before returning it to the salivette collection tube. The salivettes will be put in a portable cooler immediately after saliva collection and stored there until the end of the walk. When returning from the field, saliva samples are frozen and stored at − 20 °C until analysis. The samples will be analyzed by the laboratory of [name]. [name] at the Technical University of Dresden, Germany, to determine cortisol levels. After thawing, the samples will be centrifuged at 3,000 rpm for 5 min to obtain a clear supernatant of low viscosity. Salivary concentrations are measured using a commercially available chemiluminescence immunoassay with high sensitivity (Tecan – IBL International, Hamburg, Germany; catalog number R62111).

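### The ≥80% power for 19 groups is stated for differences between the conditions, but it was calculated only for forest versus urban built on the restoration scale

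*Protocol article*

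**What the plan says.** The Sample size calculation section opens: "A statistical power calculation was conducted for the restoration outcome scale as the primary outcome". It takes before and after ROS means from one earlier study of forest and urban built settings, simulates a mixed model with random intercepts for group and participant, and counts runs in which environment × time is significant. It concludes: "Power calculation showed that 19 groups with 1–6 participants per group are required to identify statistical differences between the conditions". The stated targets are at least 80% power and a 5% significance level. The recruitment aim follows: "we are aiming for a minimum of 10 groups in urban built environments and 10 in forests". No target is given by noise level.

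Elsewhere the scope is wider. Study design and Randomization both list the conditions as forest or urban built, each with high or low road traffic noise (a mindfulness arm is outside this protocol). H2 concerns noise overall, H3 and H4 noise within forest and within urban built settings, and RQ5 how the forest effect depends on noise. Primary outcomes names two: perceived restoration and cortisol, "measured with a self-report questionnaire and salivary cortisol as a physiological stress marker". The Background argues that "differences in the effects attributed to greenness in previous studies may also be attributed to potentially detrimental (road traffic) noise effects".

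**The concern.** The concluding sentence attaches the power to the conditions, and in this protocol that word means environment-by-noise arms. The simulation as described contains no noise term. Four of the five research questions (H2–H4, RQ5) and one of the two primary outcomes therefore have no power calculation, although the sentence reads as if the conditions were covered. With a target set only per environment, an even noise split leaves about five groups per condition, and nothing guarantees even that.

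The planning effect raises a further question. The Background says that forest–urban differences of this kind may partly be noise effects, yet the full difference is used, without discount, for a trial meant to separate the two.

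The noise question is what sets this trial apart from earlier work. A null noise result read beside a general ≥80% claim could be taken as stronger evidence of no effect than the design supports.

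**Working it through.** **Inputs from the Sample size calculation section.** ROS urban built 4.56 (SD 0.89) to 4.20 (0.97); forest 4.60 (0.84) to 5.16 (0.82); alpha 0.05; 19 groups of 1–6; minimum 10 + 10.

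**Assumptions, not in the document.** Two-sided test; mean group size 3.5; even noise split (5 groups per condition); pre-post correlation r; intraclass correlation (ICC) of change within groups; 0.46 (half of 0.92) as an illustrative noise effect.

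**Effect and SD.** Difference in change = (5.16 − 4.60) − (4.20 − 4.56) = 0.56 + 0.36 = 0.92. Pooled SD = √[(0.89² + 0.97² + 0.84² + 0.82²)/4] = √(3.111/4) = 0.88.

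**Variance of a group's mean change.** V = 2 × 0.88² × (1 − r) × [ICC + (1 − ICC)/3.5]. At r = 0, ICC 0: 1.5488/3.5 = 0.4425.

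**The plan's own figure.** At r = 0, ICC 0, 10 v 9 groups: SE = √[0.4425 × (1/10 + 1/9)] = 0.306, and 0.92/0.306 = 3.01. The noncentral t with 17 df gives 81%. Eighteen groups (9 v 9, SE 0.314, 16 df) give 79%. So 19 can be obtained, but not uniquely. Averaging over random group sizes at r = 0 gives 18 groups with SD 0.882 and 19 with 0.90. A test on unweighted group means at r = 0.3 also gives 80% at 19.

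**The other contrasts, 20 groups.** SE = √(V × 2/10) for 10 v 10 groups (H1, H2), √(V × 2/5) for 5 v 5 (H3, H4) and √(V × 4/5) for the difference between the two noise effects (RQ5). Noncentral t, 20 − 4 = 16 df.

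| | r=0, ICC 0 | r=0.3, ICC 0 | r=0.5, ICC 0 | r=0.5, ICC 0.1 |
|---|---|---|---|---|
| V | 0.4425 | 0.3098 | 0.2213 | 0.2766 |
| SE 10 v 10 | 0.297 | 0.249 | 0.210 | 0.235 |
| SE 5 v 5 | 0.421 | 0.352 | 0.297 | 0.333 |
| SE interaction | 0.595 | 0.498 | 0.421 | 0.470 |
| H1 at 0.92 (H2 the same, if noise = 0.92) | 83% | 93% | 98% | 96% |
| H2 at 0.46 | 31% | 41% | 54% | 45% |
| H3/H4 at 0.92 | 54% | 69% | 83% | 74% |
| H3/H4 at 0.46 | 18% | 23% | 31% | 26% |
| Interaction of 0.92 | 31% | 41% | 54% | 45% |
| Detectable at 80%, 10 v 10 | 0.89 | 0.74 | 0.63 | 0.70 |
| Detectable at 80%, 5 v 5 | 1.26 | 1.05 | 0.89 | 0.99 |

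The interaction SE is twice the 10 v 10 SE, so an interaction of 0.92 has the same power as H2 at 0.46.

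**Cortisol.** The document gives no effect size or SD, so power cannot be computed.

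**The case against.** The section largely discloses its scope: it names ROS, gives only forest and urban inputs, names the powered test and ends with groups per environment. A reader could take the conditions there to be the two environments. Sizing a factorial study on one main contrast and one outcome is common. All of that is fair, and it limits the point to a claim worded too widely. It does not remove it, because Study design and Randomization use the same word for the environment-by-noise arms.

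Three further limits stand. An r of 0 sits badly with a participant random intercept, which is why the table runs to 0.5. The 10 + 10 is a minimum, collected over three waves, and may be exceeded. Noise will also be modelled as a continuous measured predictor, which the 5 v 5 figures do not cover.

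A reader might infer three stronger things that the document does not support:

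- **That 19 is an arithmetic error.** It can be obtained under plausible inputs.
- **That 0.92 is inflated by noise and H1 is therefore underpowered.** The Background speaks only of potential confounding in earlier studies, and no noise data for the planning study are given.
- **That the noise contrasts are underpowered as a matter of fact.** No noise effect, r or ICC is stated. H2 equals H1 at the same effect, and H3/H4 reach 83% at 0.92 if r = 0.5 with no group variance in change. What can be said is that their power is not shown.

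**Conclusion.** The concern holds as a matter of scope: the sentence is wrong as written. The ≥80% is shown for ROS, forest versus urban built, at a difference in change of 0.92, and for nothing else. It does not carry over in general. At the minimum sample and the same 0.92, H3 and H4 range from about 54% to 83% and the interaction from about 31% to 54%, over r from 0 to 0.5 with ICC 0; an ICC of 0.1 at r = 0.5 lowers the upper ends to 74% and 45%. H2 keeps H1's power only if noise matters as much as the planned forest–urban difference. These figures rest on the even split, mean group size, r and ICC assumed above and apply to the categorical noise model. The conclusion about scope needs none of them.

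**What to change.** Replace the concluding sentence with one to this effect: *19–20 groups give ≥80% power for forest versus urban built on ROS at a difference in change of 0.92; power for the noise contrasts (H2–H4, RQ5) and for cortisol was not calculated.* State the pre-post correlation, the group variance and the group-size distribution used in the simulation, and note that 0.92 is taken undiscounted from the earlier study.

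Add the ROS differences detectable at 80% power with the minimum sample, with their assumptions: about 0.6–0.9 for 10 v 10 groups and 0.9–1.3 for 5 v 5 on the assumptions used here. Set the minimum number of groups per environment-by-noise condition (for example 5 each) instead of per environment; with a further wave planned for 2024 this can still steer recruitment.

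The cost is a less favourable power statement and a re-run of the simulation, with no extra participants.
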